##### Interviews

We will conduct formative research interviews to understand context but not to assess impact. A guide to interview participants and “Youth in Action” staff has been developed based on field work conducted in previous projects, where several of the authors participated, that studied the relation between mental health and poverty (24). The guide seeks to find the mental health resources that are available to our population and disposition to seek or recommend seeking help their willingness to participate in a mental health program. Participants and staffers will be encouraged to discuss these themes presented in the Appendix 1. The core of the discussion will be formative research that focuses on their understanding of mental health access to mental health services, and barriers/facilitators to access a mental health intervention. Questions will focus on ways to overcome stigma and recommendations on forms to generate acceptability of language related to mental health themes that will impinge on the willingness to answer our surveys. The invitations to participate in the intervention where we plan to outline the stepped care program will be co-written by JeA youth and staff to optimize engagement.

We will conduct semi-structured one-to-one interviews with 8 JeA staff to explore their experiences supporting young people with mental health issues and their views on potential barriers and facilitators to embedding the intervention in the JeA program. We will also carry 10 one-to-one interviews with young people who are beneficiaries of the JeA program to explore their views around mental health and their experiences of seeking or providing (to friends, for example) support for emotional distress and mental well-being. We will include young people enrolled in the JeA program, which will include youth with different characteristics, e.g., displaced people, victims of the armed conflict, indigenous people, and some who do not belong to any of these groups. The recruitment of these participants will be done by the regional staff of Youth in Action. They will provide us with a list of potential beneficiaries who are interested on participating and the research team will randomly select ten of them.

Once the intervention is finalized, we will also re-engage with participants to further understand the perceptions of usability, engagement, and acceptability of our program. In this initial stage, we also intend to prepare for difficulties with technology in the population we plan to engage. We have anticipated, using our most recent post-COVID national mental-health surveys, what the most present needs of this population might be. Our surveys will not be used to categorize participants to their assigned strategy but will help us complement these findings for conflict zones to potentially suggest policy initiatives to the governmental agency involved in this project.

The qualitative interviews will be recorded via Teams in video or audio, according to the participants’ preferences. Trained research team members will carry them out after informed consent is signed and before administering the questionnaires and starting the intervention. Recordings will be de-identified and kept on safe online servers.

#### Phase 2 (12 months)

Phase 2 consists of the co-design and adaptations of the proposed intervention with JeA participants. Currently, the program does not have a mental health program that caters specifically to its beneficiaries. To design the intervention, the research team will invite JeA beneficiaries and staff to three group discussions led by a facilitator and based on co-design principles and practices. Participants will be recruited using a list of beneficiaries who stated their interest in participating in qualitative research through the pre-pilot survey sent in Phase 1 Furthermore, participants who were interviewed in Phase 1 will also be invited to participate in these interactions. These sessions will enable participants to share their perspectives on mental health issues for young people in Colombia and then discuss and refine the essential features of the intervention and its delivery strategies. The guiding questions to elicit opinions and points of view will focus on the acceptability of a digital platform and encourage the use of mental health platforms available on a trial basis (Appendix 2). If no changes are possible on the digital intervention, we will listen to young people’s views about how this platform could be better delivered and use this information to adapt our intervention framework. The refined intervention will then be presented to JeA beneficiaries during a final co-design meeting to identify any more necessary adaptations. In this phase, we will also pilot the survey from which we will obtain the data.

##### Intervention development

While the digital intervention was already established, the role out and launch of the study was developed in workshops and formative interviews. Previous interventions have shown that digital initiatives have a high dropout rate and are more effective when guided by coaches. To anticipate this possibility, we will hold a virtual workshop with stakeholders (six JeA central staff and four from the FSFB) to draw a joint Theory of Change plan and a clear plan of action to launch the pilot study (Phase 3). The main stakeholders involved in the intervention development are JeA beneficiaries and staff. We will aim to conduct this work in small groups of between 4 and 8 people for staff-only and beneficiaries-only discussions and 10–15 people for joint workshops, representing all the territories involved. Team members with experience in facilitating will plan each group session. These team members will also facilitate the workshops. Potential participants will be identified and recruited with the help of JeA staff members.

#### Phase 3 (18 months)

During Phase 3, we will pilot the intervention to determine its feasibility, acceptability, efficacy, and usefulness in ‘real settings’. Results will inform if the intervention improves clinical, educational and employment prospects among those who use it. A sample of beneficiaries studying in our areas of interest will be invited to participate in a survey containing measures of mental health human capital. All those beneficiaries scoring above cut-off points will be automatically invited to access the intervention, and anyone suspected at risk will be offered support and referral to health services.

##### Intervention

The study will pilot a stepped-care mental health program that aims to be structured, brief and includes evidence-based components. The digital intervention will not be developed by the research team. Instead, we will use a third-party platform (SilverCloud®) a virtual mental health platform with eight modules with different tools for comorbid depressive and anxiety symptoms. This platform has been adapted for use by student populations that mainly attend private universities in Colombia and has proven to be effective (25).

This program is designed to facilitate the participants’ social and labor insertion. The intervention will target depression, anxiety, PTSD, and comorbidities. Participants from the intervention sites will be classified in four levels of severity (asymptomatic, mild, moderate, and severe) according to their scores in these three dimensions encompassing access to a mental-health digital platform and individualized care. They will be offered differential attention strategies (see Figure 2). We will use a transdiagnostic stepped-care intervention program, in which three levels of attention will be in place to respond to the severity of the symptoms as determined by three screening questionnaires encompassing access to a mental-health digital platform and individualized care. This strategy has been planned to provide individualized care for those in severe conditions and considering the high degree of comorbidity documented in conflict zones. The protocol also considers the number of sessions we anticipate will be amenable to our participants. Participants with moderate and mild symptoms will also have access to the digital platform. People with moderate symptoms will have a coach to monitor their progress while the platform is available; people with mild conditions will only be offered the platform. Unlike previous mental health initiatives, we intend to ascertain how to foster the acceptability of a digital strategy, in our initial co-design phase, and the acceptability of personalized virtual sessions with our psychologists.

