**Figure 2 fig2:**
[figure not shown]
Flow chart of strategies offer within the stepped-care mental health program intervention sites to four levels of severity (asymptomatic, mild, moderate, and severe).

Asymptomatic participants will receive an email with online resources and tools to help them manage their mental health, and they will not be included as part of the study. The online resources are digital health and psychoeducation platforms that are available nationally and are part of the social outreach initiatives of the Fundación Santa Fe de Bogota. Participants with mild symptoms will receive access to SilverCloud®, a virtual mental health platform with eight modules with different tools for comorbid depressive and anxiety symptoms (26). This platform has been adapted for use by student populations that mainly attend private universities in Colombia, and has proven to be effective (25). The access to the web-based platform will be self-guided. They will also receive an invitation to participate in a mental health workshop in their territories.

For participants with moderate symptoms, the platform will also be available, but in addition, asynchronous feedback will be provided by trained guides (27). The asynchronous feedback will consist of motivational messages as the participants progress through the different modules. The platform also offers participants the opportunity to send messages to the guide and for the guide to respond. Those with severe symptoms will also access SilverCloud® with asynchronous feedback and receive a person-centered intervention delivered by trained psychologists face-to-face or virtually, depending on the participant’s choice.

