#### Inclusion criteria

For all parts of the study, participants must be adults aged 18–28 and registered with the public social program (JeA) living in seven Colombian municipalities affected by the armed conflict. These 7 municipalities are part of the 170 municipalities categorized as “The Development Programs with a Territorial Approach” (PDET in Spanish) by the Havana peace agreement to prioritize social and economic development programs and are the areas most hardly hit by the armed conflict. JeA users are characterized by their low socioeconomic status, according to the National Social Services’ criteria. Many of them are victims of the armed conflict as defined by the victims’ law in Colombia. Participants who meet the inclusion criteria and present anxiety, depression, or post-traumatic stress disorder symptoms will be invited to participate in Phase 3 – piloting the mental health intervention.

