#### Study design

Our study is based on a cross-over design, whereby participants in three treatment municipalities (Florencia, Santa Marta, and Valledupar) will be offered the intervention, while participants in four control municipalities (Apartadó, Buenaventura, Ciénega, and San Andrés de Tumaco) will serve as control. Due to ethical reasons, we must offer the intervention to beneficiaries in the control municipalities following the period of intervention in the treatment group. Control municipalities will thus receive the intervention once the two post-treatment measures are taken.

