### Questionnaire instruments

We will invite all students across the selected PDET municipalities to complete the mental health and human capital survey. The following tools will be used to determine the severity of mental health symptoms and human capital outcomes. (1) *Patient Health Questionnaire – PHQ-9*, which is widely used to assess depression symptoms (28), has been validated for use in Colombia (29, 30) and with low income, limited education populations in rural areas with good results (31, 32). Its internal consistency is 0.80. (2) Anxiety will be assessed with GAD-7 (33). Its internal consistency is 0.90, sensitivity 0.92, and specificity 0.83. (3) A Post-traumatic stress disorder brief screen will also be included PC-PTSD-5 (34). It has a test–retest reliability of 0.83, sensitivity with a score of 3 has a sensitivity of 0.93 m specificity is 0.94. (4) Two questions from the Insomnia Severity Index (35, 36), with a reliability of 0,86, sensitivity of 0.87. (5) AF5 Self-Concept Questionnaire (6) Rosenberg Self-esteem scale (RSE) (37). These questionnaires are widely used by studies where the efficacy of interventions that use digital platforms are examined.

In terms of short-term/immediate assessment of the potential of the intervention to improve human capital, we will look at: school attendance (using administrative data on academic enrolment reports), educational permanence (using administrative data on academic permanence reports, every six months), and academic performance (using administrative data on academic excellence report, every six months). Based on data directly collected as part of the pilot intervention, we will also assess the short-term efficacy of the number of hours spent on average during the past academic period studying weekly, the number of hours that beneficiaries dedicate in this academic period to study weekly and the self-reported grade point average in current and past academic periods. In terms of the longer-term efficacy of the intervention, we will look at: certification (whether completed educational program, based on JeA administrative records) and formal labor market inclusion (whether working in a formal job, based on PILA Administrative Registry). Furthermore, we will also assess the efficacy of the mental health intervention on self-esteem (RSES) and self-concept (AF5).

Figure 3 summarizes the estimated length, activities, and instruments used in each of the phases.

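### The protocol disagrees with itself on whether controls must be symptomatic at baseline; if they need not be, regression to the mean would look like benefit on the symptom scales

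*Protocol article*

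**What the plan says.** All references are to the protocol article.

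**Pointing to selection in the intervention sites only**
- Intervention: "Participants from the intervention sites will be classified in four levels of severity (asymptomatic, mild, moderate, and severe".
- Text below Figure 2, whose caption is limited to intervention sites: asymptomatic respondents are sent online resources and "they will not be included as part of the study".
- Phase 3 (18 months): "All those beneficiaries scoring above cut-off points will be automatically invited to access the intervention". The cut-off triggers an invitation to treatment; no separate rule says who enters the control group.
- Study design: "participants in four control municipalities (Apartadó, Buenaventura, Ciénega, and San Andrés de Tumaco) will serve as control", with no symptom condition. The closing paragraph of the Intervention section, on what controls receive after the measures, gives none either.

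**Pointing to selection everywhere**
- Inclusion criteria: these apply to people "registered with the public social program (JeA) living in seven Colombian municipalities affected by the armed conflict", which is the three treatment plus four control municipalities. The section continues: "Participants who meet the inclusion criteria and present anxiety, depression, or post-traumatic stress disorder symptoms will be invited to participate in Phase 3", and describes that phase as piloting the intervention.

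**Data and analysis**
- Questionnaire instruments: "We will invite all students across the selected PDET municipalities to complete the mental health and human capital survey".
- Screening questionnaire: the survey is given before the intervention, immediately after it and three months later.
- Quantitative analysis of impact: difference-in-differences between treatment and control areas, plus an effectiveness outcome defined as the share of participants whose symptoms fall from baseline. Nothing there limits the controls analysed to symptomatic respondents.

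**The concern.** The PHQ-9, GAD-7 and PC-PTSD-5 scores that decide who counts as symptomatic are also the pre-intervention values in the analysis of change. People chosen because they scored high on one occasion score lower on average on the next, treated or not. If both groups are chosen by the same rule, this fall is largely shared and cancels. If only the treated group is chosen that way, it does not cancel.

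The protocol relies on difference-in-differences to remove time-invariant differences between areas. Regression to the mean is not such a difference: it is a change over time created by selection in one group. The error would always favour the intervention. The outcome based on any reduction is exposed as well, and a control who scores zero at baseline cannot show a reduction at all.

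**Working it through.** **1. The planned effect as yardstick.** The Sample size section gives d = 0.25 (f = 0.125), 5% significance, 80% power and 501 participants. For two groups, 2 × (1.96 + 0.842)² / 0.25² = 251.2, so 252 per group and 504 in total, within 3 of 501. This is an unclustered two-group calculation. It confirms that 0.25 is a standardised two-group difference, which is all that is needed here; the point does not depend on the sample size.

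**2. Inputs**
- From the protocol (Mental health interventions for conflict victims): prevalence of depression 43%, anxiety 52%, PTSD 11–47%.
- From the protocol (Questionnaire instruments): test–retest reliability 0.83, given for the PC-PTSD-5 only.
- Assumed: PTSD prevalence 30%; correlation r between baseline and endline of 0.6 to 0.83 on each scale; depression–anxiety correlation 0.6–0.7; PTSD correlation 0.5 with each; normal scores; no treatment effect.

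**3. Selection on one scale, closed form.** With a share p above cut-off c, the expected fall in the selected group is (1 − r) × φ(c)/p SD, and in an unselected group it is 0.
- p = 0.43: φ(c)/p = 0.393/0.43 = 0.913. The fall is 0.17 × 0.913 = 0.155 SD at r = 0.83, 0.3 × 0.913 = 0.27 at r = 0.7, and 0.4 × 0.913 = 0.37 at r = 0.6.
- p = 0.52: φ(c)/p = 0.398/0.52 = 0.766. The falls are 0.13, 0.23 and 0.31 SD.

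These values are too high for this trial, because eligibility needs symptoms on any one of three scales.

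**4. Selection on any of three scales, by simulation.** Three correlated scores were drawn at two times, respondents above the cut-off on any scale at time 1 were kept, and the mean change was taken.
- About 66% are kept. The spurious fall on PHQ-9 or GAD-7 is about 0.07 SD at r = 0.83 and up to 0.20 SD at r = 0.6. Against the planned effect that is 0.07/0.25 = 28% to 0.20/0.25 = 80%.
- With one common between-scale correlation of 0.5 to 0.7 instead, 63–68% are kept and the fall on depression is 0.07–0.21 SD.
- With very low cut-offs (70% positive on each scale, 89% kept), the fall is 0.03–0.07 SD at r = 0.8 to 0.6.
- With errors independent across scales, it is 0.04–0.09 SD at r = 0.8 to 0.7.
- The share showing any reduction in depression score is about 55–59% in the selected group and 50% in an unselected one, under the main error assumption.

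**5. Same rule in both groups.** If one cut-off is applied in all seven municipalities and the baseline distributions are alike, the expected fall is equal in both groups and the false difference is about 0.

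**The case against.** The strongest reply is that eligibility is set under Inclusion criteria, not under Intervention. Those criteria open by covering all parts of the study, take in all seven municipalities, and require symptoms for Phase 3. Controls are offered the intervention later, so describing Phase 3 as piloting the intervention does not put them outside that rule. The sentence removing asymptomatic people speaks of the study, not of one arm, and the Discussion describes the target group as students with symptoms. The four severity levels also have an ordinary purpose: they assign people to a care step, which controls do not need.

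Most of this stands. A reader might infer from the Intervention and Study design sections that the protocol plans to compare selected treated participants with unselected controls. The document does not support that: no section says so, and the inclusion criteria point the other way. A reader might also infer that comparison by severity level is impossible. That is not supported either, because the survey covers all selected municipalities and the levels can be derived for controls from their baseline scores. The human-capital outcomes are not themselves selected on, so the calculated bias does not carry over to them directly.

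What the reply does not remove is the conflict. The survey that measures symptoms is itself part of Phase 3, so the symptom condition cannot govern entry to the whole phase. It can be read as governing only the invitation to treatment, which is how the Phase 3 section words it. The composition of the comparison groups is a core rule that the article does state, in ways that do not agree.

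**Conclusion.** The concern holds as a conflict between sections on whether the control cohort is symptom-selected, not as a stated plan to use unselected controls. If the one-sided wording were followed, the symptom-scale estimates would be biased towards the intervention by roughly 0.07–0.20 SD for selection on any scale, against a planned d of 0.25, and the share with a reduction would be about 55–59% against 50%.

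The size rests on assumed correlations and cut-offs, since the protocol gives no retest figure for PHQ-9 or GAD-7. It is smaller with very low cut-offs or errors independent across scales. The direction does not depend on these choices. The matter should be settled before the analysis set is formed, because it decides who enters the main comparison.

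**What to change.** Reconcile Phase 3, Intervention (including the text below Figure 2), Inclusion criteria, Study design and Quantitative analysis of impact by stating three things:

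1. The same baseline cut-offs on the three screening questionnaires define the study cohort in all seven municipalities.
2. Asymptomatic respondents are excluded from the analysis in control and intervention municipalities alike.
3. The difference-in-differences analysis is run on that common cohort.

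Baseline severity level, derived by the same rule in both groups, can then be used for stratified comparisons. This concerns who is analysed, not what care anyone is offered.

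The cost is a few sentences, with no new data collection. The one downside is that some surveyed controls no longer count towards the control sample.

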**Figure 2 fig2:**
[figure not shown]
Flow chart of strategies offer within the stepped-care mental health program intervention sites to four levels of severity (asymptomatic, mild, moderate, and severe).

Asymptomatic participants will receive an email with online resources and tools to help them manage their mental health, and they will not be included as part of the study. The online resources are digital health and psychoeducation platforms that are available nationally and are part of the social outreach initiatives of the Fundación Santa Fe de Bogota. Participants with mild symptoms will receive access to SilverCloud®, a virtual mental health platform with eight modules with different tools for comorbid depressive and anxiety symptoms (26). This platform has been adapted for use by student populations that mainly attend private universities in Colombia, and has proven to be effective (25). The access to the web-based platform will be self-guided. They will also receive an invitation to participate in a mental health workshop in their territories.

For participants with moderate symptoms, the platform will also be available, but in addition, asynchronous feedback will be provided by trained guides (27). The asynchronous feedback will consist of motivational messages as the participants progress through the different modules. The platform also offers participants the opportunity to send messages to the guide and for the guide to respond. Those with severe symptoms will also access SilverCloud® with asynchronous feedback and receive a person-centered intervention delivered by trained psychologists face-to-face or virtually, depending on the participant’s choice.

A group of local psychologists will be trained on different evidence-based tools for depression and anxiety. The training will be done through virtual sessions, and they will receive a manual (developed by the research team on Phase 2) with a step-by-step guide on the intervention. A pre-pilot of the intervention will be done with 10–15 participants with severe scores to supervise adherence to the manual from the psychologists and adjust the protocol, if needed. The intervention is based on CBT and transdiagnostic techniques. It consists of up to five face-to-face or online sessions in which participants will be offered one introduction session with psychoeducation of depression and anxiety from a CBT approach, and at least two psychological tools depending on their symptoms. These tools will include problem-solving, behavioral activation, strengthening of social support, and reduction of safety behaviors. Psychologists will access the participant’s screening scores and progress in SilverCloud® and choose the tools depending on what they observe in the first session. Participants will also receive a workbook containing infographic material on each tool that may be suggested for use by the participants by the psychologists during individualized sessions. Additionally, psychologists will regularly meet with a clinical psychiatrist to discuss participants’ progress.

This strategy has been planned to provide individualized care for those in severe conditions and considering the high degree of comorbidity documented in conflict zones. The protocol also considers the number of sessions we anticipate will be amenable to our participants. Unlike previous mental health initiatives, we intend to ascertain how to foster the acceptability of a digital strategy, and the acceptability of personalized virtual sessions with psychologists.

Participants from the control groups will not receive the intervention until the measures are completed. Afterwards, they will receive access to SilverCloud® (self-guided) and an email with mental health promotion tools. Those who are at risk and need specialized mental health attention (e.g., those with suicidal risk) will be referred to the psychologist of their institutions.

The intervention lasts 16 weeks (4 months), approximately. Phase 3 also includes: one month of recruitment and meetings with the universities and staff from each territory, baseline interview, intervention, endline interview (immediately after the intervention, open for a couple weeks while we reach the target number of participants), follow up (3 months after the deadline), data analysis and presentation of results to the territories.

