### Digital mental health interventions in Colombia

There are few studies on the feasibility and impact of digital mental health interventions in Colombia. A recent study of an internet intervention for college students, assisted by a trained person, showed positive results but high dropout rates (around 80%) (19). Members of our team have developed and tested several simple mental health digital tools with good adherence and outcomes in other Latin American countries (20–23). With the advent of the COVID-19 epidemic, remote delivery is an additional underexplored challenge that this project aims to address. This study is particularly unique in that we work directly with Government within a public program. So far, no studies have assessed the impact of incorporating a mental health intervention within an existing public cash transfer program to address poverty.

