### Study design, sample, and recruitment

#### Sample size

As a pilot study with no pre-specified effect size hypothesis, it is not relevant to estimate a sample size for hypothesis testing. However, to carry out preliminary analysis of impact, we defined the sample size as follows: assuming an intraclass correlation coefficient of 0.04, an effect size of 0.125 (index f) equivalent to Cohen’s d = 0.25, with a significance level of 5% and a statistical power of 80%, the minimum sample required would be 501 participants (167 per site, of three locations). Our goal is to recruit a minimum of 170 participants from each site, given an expected moderately high attrition rate.

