### Quantitative analysis of impact

Our primary aim will be to assess the impact of the intervention on our mental health and human capital outcomes. We will use regression analysis with a difference-in-differences design, which compares changes in outcomes before and after intervention measures across participants in treatment and control areas. This approach considers human capital as an outcome embodied in individuals by exploring the variation in individual knowledge (cognitive skills captured by academic performance) and individual abilities (non-cognitive skills acquired as life competencies). Thus, we will look at the magnitude of mental health-based rehabilitation on young adult students across different dimensions of mental health (depression and anxiety, fundamentally), which is considered beneficial due to human capital accumulation.

Since individual observations will be collected in different regions, we will adjust for clustered data. In the absence of treatment randomization that assures that treatment and control groups are exchangeable, this quasi-experimental design helps us to control for time-invariant differences between treatment and control areas by focusing on changes, rather than levels, in outcomes. To address bias from time-varying confounders, we will incorporate controls for time-varying factors in all analyses. We will all report the prevalence of depression, anxiety, and PTSD, along with their commodities and the effectiveness outcome, which will be the proportion of participants with a reduction in their baseline symptoms. To determine the changes in human capital, we will use both administrative and survey data that measure continued JeA program enrolment, accumulated grade point average, and self-reported hours dedicated to study. This will be carried out in STATA-19.

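### The endline survey window is tied to a target count rather than to everyone measured at baseline, and the stated conclusion is about users while the comparison is by offer and area

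*Protocol article*

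**What the plan says.** All references are to the protocol article.

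- **Endline window.** The last paragraph under Intervention sets out Phase 3 and includes the "endline interview (immediately after the intervention, open for a couple weeks while we reach the target number of participants"). A further measurement follows three months later, with no count attached.
- **Stated conclusion.** Phase 3 says: "Results will inform if the intervention improves clinical, educational and employment prospects among those who use it". The Methods part of the Abstract repeats this.
- **Treatment condition.** Under Study design, participants in three municipalities "will be offered the intervention, while participants in four control municipalities" serve as comparators. Controls get access only after both post-treatment measures.
- **Analysis.** Quantitative analysis of impact plans a difference-in-differences regression that "compares changes in outcomes before and after intervention measures across participants in treatment and control areas". On bias it says that "this quasi-experimental design helps us to control for time-invariant differences between treatment and control areas", and it adds controls for time-varying factors. The effectiveness outcome is "the proportion of participants with a reduction in their baseline symptoms".
- **Planned effect.** Sample size assumes "an effect size of 0.125 (index f) equivalent to Cohen’s d = 0.25".

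**The concern.** Two stated features fit poorly with the planned comparison.

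The first is the endline window. A window linked to a number of respondents lets the analysed sample be shaped by how quickly people answer, which is behaviour after treatment. Difference-in-differences removes fixed differences in level between areas, and covariates remove what they measure. Neither removes response that depends on a participant's own improvement, if that dependence differs by arm. There is a reason for it to differ. Over about 16 weeks treated participants have the platform, and those with moderate or severe symptoms also have guide messages or psychologist sessions. Controls have no such contact from the study before endline. The effectiveness outcome is a proportion, and it can be computed only for people who return an endline value.

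The second is the target of inference. A conclusion about users answers a different question from a comparison by municipality offer, and controls have no counterpart to use before endline.

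Without randomisation, the analysis depends on the endline sample representing the baseline sample to the same degree in both arms.

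**Working it through.** **1. The benchmark.** For two groups, f = d/2, so d = 0.25 gives f = 0.125, as stated. With 5% two-sided (sidedness is not stated) and 80% power, n per arm = 2 × (1.960 + 0.842)² / 0.25² = 251.2, rounded up to 252. The total is 504, against the 501 stated under Sample size. This match leaves out the stated intraclass correlation, which is a separate matter. Here 0.25 serves only as the yardstick.

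**2. How far attrition could bite.** The plan recruits 170 per site for a minimum of 167, which covers 1 − 167/170 = 1.8% loss, while expecting attrition it calls moderately high. The article does not define the endline target. If it were 167 per site, 30% attrition would need 167/0.7 = 239 recruits and 50% would need 167/0.5 = 334. So either the count is missed, or it is filled from a larger baseline pool by those who answer.

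**3. Selection within one arm.** Suppose a share r of an arm responds, and the correlation between propensity to respond and improvement is ρ (bivariate normal). Mean change among respondents then differs from the arm's true mean change by

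shift = ρ × φ(z_r) / r, with z_r = Φ⁻¹(r), in SDs of change.

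The ratio φ(z_r)/r is 0.497 at r = 0.7 and 0.798 at r = 0.5. Both r and ρ are assumptions; the document gives neither.

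| Response r | ρ = 0.1 | ρ = 0.3 | ρ = 0.5 |
|---|---|---|---|
| 70% | 0.05 | 0.15 | 0.25 |
| 50% | 0.08 | 0.24 | 0.40 |

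**4. What reaches the difference-in-differences.** Bias = shift in treated arm − shift in control arm.

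- Equal r and ρ in both arms: bias = 0.
- Selection in the treated arm only: the table values.
- In between, 70% response in both arms, ρ = 0.3 treated and 0.1 control: 0.149 − 0.050 = 0.10.
- Same correlations at 50% response: 0.239 − 0.080 = 0.16.

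These are SDs of change. They compare directly with d = 0.25 only if the SD of change equals the SD behind d; with equal SDs at both times, that needs a baseline–endline correlation of 0.5.

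**5. Which outcomes are exposed.** Under Questionnaire instruments, attendance, permanence, academic performance, certification and formal employment come from administrative records, so endline survey response does not determine them. Exposed are the symptom scales, self-esteem, self-concept and self-reported study measures at endline.

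**6. Conclusion against comparison.** Phase 3 and the Abstract speak of users. Study design defines treatment by offer. Quantitative analysis of impact compares participants by area and nowhere restricts them to users. The stated conclusion and the stated comparison are therefore different quantities.

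**The case against.** The best defence is that the article's wording is loose rather than wrong. The window is given as a couple of weeks, and the phrase may mean that it is held open to raise response. Nothing says that the survey closes early, that sites close at different times, or that some baseline participants are not contacted. That stands: the wording permits selection by speed of response but does not prescribe it. The window also is not confined to one arm, and equal selection cancels.

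A reader might go further and infer that users in treated sites will be set against all controls. No section plans this. The reference to users is a statement of aim, and the analysis text compares by area.

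A reader might also carry over the roughly 80% dropout cited for another Colombian internet intervention. The article does not say that this was survey non-response, and it is no forecast of endline response here.

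Nor can the bias be called upward. Those with severe symptoms get the most contact, and who then answers cannot be read from the document.

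Finally, methods for missing data and formal analysis populations may be left to a fuller plan, and their absence is not the point. What remains is a stated collection rule and a stated conclusion, both poorly matched to the stated analysis.

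**Conclusion.** The point holds in a limited form. The endline window is linked to a count, and the planned difference-in-differences does not protect the survey outcomes at endline if response relates to improvement differently by arm. The size is conditional: zero under equal selection, about 0.05 to 0.25 SD of change at 70% response and 0.08 to 0.40 SD at 50% if selection acts in the treated arm only, for assumed correlations of 0.1 to 0.5. The planned effect is 0.25, so selection confined to one arm could rival it, but the document gives no evidence that it would. The direction is unknown, and administrative outcomes are not affected. Separately, the conclusion about users does not match the comparison by offer and area, and the two need reconciling. Both are worth changing mainly because the change is cheap.

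**What to change.** - Use one fixed endline window of the same length in all seven municipalities. Contact every symptomatic baseline participant in both arms, and do not close on a count.
- Keep the difference-in-differences on all of these participants, by municipality offer and regardless of use. Report endline response by arm.
- In Phase 3 and the Abstract, word the conclusion as benefit among those offered the intervention.
- Treat any result among users as descriptive only. Using municipality offer as an instrument for use is not recommended: the offer was not randomised, and it also brings workshop invitations and psychologist sessions, so it can act other than through platform use.

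The cost is a few more reminders on an online survey that already exists, plus small wording changes. The downside is that the effect of the offer will be smaller than an effect among users.
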